## Abstract

**Background:**

The Prophylactic hypOthermia to Lessen trAumatic bRain injury-Randomised Controlled Trial (POLAR-RCT) will evaluate whether early and sustained prophylactic hypothermia delivered to patients with severe traumatic brain injury improves patient-centred outcomes.

**Methods:**

The POLAR-RCT is a multicentre, randomised, parallel group, phase III trial of early, prophylactic cooling in critically ill patients with severe traumatic brain injury, conducted in Australia, New Zealand, France, Switzerland, Saudi Arabia and Qatar. A total of 511 patients aged 18–60 years have been enrolled with severe acute traumatic brain injury.

The trial intervention of early and sustained prophylactic hypothermia to 33 °C for 72 h will be compared to standard normothermia maintained at a core temperature of 37 °C.

The primary outcome is the proportion of favourable neurological outcomes, comprising good recovery or moderate disability, observed at six months following randomisation utilising a midpoint dichotomisation of the Extended Glasgow Outcome Scale (GOSE). Secondary outcomes, also assessed at six months following randomisation, include the probability of an equal or greater GOSE level, mortality, the proportions of patients with haemorrhage or infection, as well as assessment of quality of life and health economic outcomes. The planned sample size will allow 80% power to detect a 30% relative risk increase from 50% to 65% (equivalent to a 15% absolute risk increase) in favourable neurological outcome at a two-sided alpha of 0.05.

**Discussion:**

Consistent with international guidelines, a detailed and prospective analysis plan has been developed for the POLAR-RCT. This plan specifies the statistical models for evaluation of primary and secondary outcomes, as well as defining covariates for adjusted analyses and methods for exploratory analyses. Application of this statistical analysis plan to the forthcoming POLAR-RCT trial will facilitate unbiased analyses of these important clinical data.

**Trial registration:**

ClinicalTrials.gov, NCT00987688 (first posted 1 October 2009); Australian New Zealand Clinical Trials Registry, ACTRN12609000764235. Registered on 3 September 2009.

**Electronic supplementary material:**

The online version of this article (10.1186/s13063-018-2610-y) contains supplementary material, which is available to authorized users.

## Background

Traumatic brain injury (TBI) is a leading cause of mortality and long-term disability, particularly affecting young people. Even a small increase in the number of TBI victims who are able to live independently, instead of being permanently disabled, would yield major human and economic benefits [1, 2].

The application of *early prophylactic* hypothermia [3] involves the rapid reduction after injury of core body temperature to 33 °C. This therapy has shown promise as an intervention to attenuate TBI [4], with the distinctly early cooling intervention design of the Prophylactic hypOthermia to Lessen trAumatic bRain injury-Randomised Controlled Trial (POLAR-RCT; randomisation within 3 h of estimated time of injury) contrasting with a recent unsuccessful cooling intervention (*therapeutic* hypothermia) applied mostly 12 h or more after TBI [5, 6]. POLAR-RCT is an international, multicentre, randomised, parallel group phase III superiority trial of prophylactic hypothermia delivered to adult critically ill patients with acute severe TBI (Glasgow Coma Score [GCS] < 9) [7]. Despite a recent meta-analysis [8] suggesting improved neurological outcomes from TBI associated with therapeutic hypothermia to 33 °C for 72 h, substantial clinical uncertainty remains in this field [9]. POLAR-RCT aims to evaluate six-month survival and neurological function in adult patients with severe TBI randomised to early prophylactic hypothermia to 33 °C, compared to normothermia.

## Methods/Design

### Study design and definitions

The POLAR-RCT is a multicentre, prospective, two parallel groups, randomised phase III superiority trial evaluating the safety and efficacy of early prophylactic hypothermia targeting a core temperature of 33 °C in adult ICU patients with severe TBI using clinically available refrigerated vests, wraps, jackets, or blankets [7]. Control patients received protocol-directed temperature adjustment, using similar equipment if necessary, to maintain normothermia, defined as a core temperature of 36.5–37.5 °C. Patients enrolled in both the hypothermia and normothermia groups have been managed according to current international evidence-based guidelines [10]. Patient randomisation completed on 10 November 2017 with a total of 511 participants and final collection of all six-month outcome data is anticipated by June 2018.

### Treatment masking (blinding)

Patient temperature is a key clinical vital sign and therefore it is not possible to blind clinical staff to treatment allocation. Bias will be minimised by concealed treatment allocation before randomisation, by protocolised treatment in both groups [7] and by assessment of the primary outcome by centralised, blinded and trained research staff (as accomplished successfully in recent studies including SAFE [11], SAFE-TBI [12], HTS [13] and ATBIS [2]). The primary outcome measure (neurological outcome at six months from randomisation, see below) is subject to minimal ascertainment bias.

### Compliance with good clinical practice

The trial is being conducted, and accumulating data monitored, according to the standard requirements of Good Clinical Practice [14]. Data are collected by trained staff at each study site and entered into a secure, password-protected, encrypted web-based data collection form. Queries of potential inconsistencies are generated automatically by the trial website to facilitate early resolution. Data are stored in a secure server operated by Monash University; data management will be performed by the Clinical Informatics and Data Management Unit, Monash University, Melbourne, Australia [15]. Site monitoring will be performed at each participating hospital by the Trial Project Manager to ensure the study is conducted according to the protocol and all applicable regulations, and to perform source data verification (Additional file 1).

General confidence in the final results and conclusions of clinical trials is enhanced when the statistical approaches to outcome analyses are specified before the availability of trial data. The following statistical analysis plan complies with recommendations for the Consolidated Standards of Reporting Trials (CONSORT) (Fig. 1) [16, 17], the Standard Protocol Items: Recommendations for Interventional Trials (SPIRIT) (Fig. 2) [18, 19] (and checklist as an Additional file 2) as well as guidance from the International Conference on Harmonisation of Technical Requirements for Registration of Pharmaceuticals for Human Use, especially ‘Statistical principles for clinical trials E9’ [20] and ‘Structure and content of clinical study reports E3’ [21].

**Fig. 1 Fig1:**
[figure not shown]
Consort *diagram*

**Fig. 2 Fig2:**
[figure not shown]
SPIRIT *figure*

This statistical analysis plan identifies the procedures to be applied to the primary and secondary outcome analyses once trial data validation is complete. Covariates for adjusted analyses and selected subgroups of interest are also pre-specified. This plan defines the intention-to-treat (ITT) full analysis set, as well as exploratory analyses in ‘as-treated’ and ‘per-protocol’ subsets, accompanied by an analysis seeking to estimate the average causal effect of cooling in the presence of non-compliance with the cooling intervention [22].

### Trial population and eligibility

A total of 511 severe TBI patients have been enrolled in Australia, New Zealand, France, Switzerland, Saudi Arabia and Qatar. This 511-patient full analysis set will not include the initial eight patients who were treated within a pre-trial run-in phase. Fourteen emergency departments and five pre-hospital agencies were involved. Patients may have been enrolled in the pre-hospital setting, if specifically trained and qualified staff are available, or by medical staff in the emergency department of participating hospitals. The inclusion and exclusion criteria are presented in Table 1. Eligible patients were randomised to receive prophylactic hypothermia (33 °C for 72 h) or TBI care that is standard (for that hospital) (Figs. 1 and 2).

**Table 1 Tab1:** Inclusion and exclusion criteria

Pre-hospital inclusion criteria	Emergency Department inclusion criteria
• Blunt trauma with clinical diagnosis of severe TBI and GCS < 9 • Estimated age ≥ 18 and < 60 years • The patient is intubated or intubation is imminent	• Blunt trauma with clinical diagnosis of severe TBI and GCS < 9 • Estimated age ≥ 18 and < 60 years • The patient is intubated or intubation is imminent
Pre-hospital exclusion criteria	Emergency Department exclusion criteria
• Clinical diagnosis of drug or alcohol intoxication as predominant cause of coma • Randomisation unable to be performed within 3 h of estimated time of injury • Estimated transport time to study hospital > 2.5 h • Able to be intubated without drugs • Systolic BP < 90 mmHg • Heart rate > 120 bpm • Cardiac arrest at the scene or in transit • GCS = 3 + un-reactive pupils • Penetrating neck/torso injury • Known or obvious pregnancy • Receiving hospital is not a study site • Evidence of current anti-coagulant treatment Known to be carer dependent due to a pre-existing neurological condition	• Clinical diagnosis of drug or alcohol intoxication as predominant cause of coma • Randomisation unable to be performed within 3 h of estimated time of injury • Able to be intubated without drugs • Persistent systolic BP < 90 mmHg • GCS = 3 + un-reactive pupils • Cardiac arrest at the scene or in transit • Clinically significant bleeding likely to require haemostatic intervention, for example: ○ Bleeding into the chest, abdomen or retro-peritoneum likely to require surgery ± embolisation ○ Pelvic fracture likely to require surgery ± embolisation ○ More than two long bone fractures requiring operative fixation • Penetrating neck/torso injury • Positive urine or blood pregnancy test • Evidence of current anti-coagulant treatment • Known to be carer dependent due to a pre-existing neurological condition • In the treating clinician’s opinion, ‘cooling’ is not in the patient’s best interest

### Randomisation

Randomisation 1:1 between trial hypothermia and normothermia was performed by paramedics or physicians using sequentially numbered, opaque, sealed envelopes (as used in the RICH [23] and RSI trials [24]), printed at the Australian trial coordinating office before distribution to sites. Envelopes were used because at the time of trial design it was not feasible to develop a centrally controlled, real-time electronic randomisation system across international emergency departments and pre-hospital ambulances services. The computer-generated randomised treatment allocation schedule (using Stata version 11 *ralloc* module http://fmwww.bc.edu/repec/bocode/r/ralloc.ado) [25] was stratified by hospital group or pre-hospital paramedic ambulance service with a permuted block scheme. Hospital strata were defined for participating hospitals in nine groups, comprising three Australian states (Victoria, Queensland, Western Australia), two localities in New Zealand (Auckland, Waikato) and four other countries (France, Switzerland, Saudi Arabia, Qatar). Stratification of pre-hospital randomisation schedules was also specified within the four networks where such enrolment was possible (Queensland, Victoria, Western Australia, France) (Table 2).

**Table 2 Tab2:** The count of strata incorporated within the block-randomised 1:1 hypothermia / normothermia treatment allocation schedule

Pre-hospital	Stratum no.	Hospital region	Stratum no.
Yes^a^	1	Victoria^a^	5
Yes^a^	2	Western Australia^a^	6
Yes^a^	3	Queensland^a^	7
Yes^a^	4	France^a^	8
No		Switzerland	9
No		Saudi Arabia	10
No		Qatar	11
No		Auckland	12
No		Waikato	13

^a^Participating pre-hospital ambulance services and their relevant regional hospitals within each of these Australia states and France were each included as separate strata within the computerised generation of randomisation envelopes

Patients who fulfilled the inclusion criteria and had no exclusion criteria were randomised by opening the next available opaque envelope within the ambulance or hospital emergency room.

In the pre-hospital setting patients were assessed by study trained and affiliated ambulance paramedics and/or physicians. Patients who were enrolled in the study by a pre-hospital agency were assessed for study suitability and continuance on arrival in the first participating emergency department. Patients who were not enrolled in the study by a pre-hospital agency were assessed for study suitability on arrival in the associated hospital emergency department.

### Study objectives and endpoints

#### Primary outcome

The primary outcome will be each patient’s neurological outcome at six months from randomisation. This is defined from a standard mid-point dichotomisation of the eight level ordinal Extended Glasgow Outcome Scale (GOSE) [26] (Table 3), with favourable outcomes comprising lower moderate disability (GOSE 5) through upper good recovery (GOSE 8) and unfavourable outcomes comprising death (GOSE 1), the vegetative state (GOSE 2) or severe disability (GOSE 3 to 4).

**Table 3 Tab3:** The eight-level ordinal Extended Glasgow Outcome Scale (GOSE)

Score	Description	Code
1	Dead	D
2	Vegetative state	VS
3	Lower severe disability	SD -
4	Upper severe disability	SD +
5	Lower moderate disability	MD -
6	Upper moderate disability	MD +
7	Lower good recovery	GR -
8	Upper good recovery	GR +

#### Secondary outcomes

Secondary outcome measures are:GOSE regarded as an ordinal variable (as opposed to the dichotomisation used as the primary outcome variable)Quality of life (QOL) assessments at six months:○ EQ5D3L [27]○ SF12 [28]Complier average causal effect of hypothermia on GOSE at six months comparing hypothermia and control patientsMortality (all cause) at:○ hospital discharge○ six monthsProportion of patients with adverse events (AEs) within ten days of randomisation, specifically:○ bleeding (intracranial, extracranial)○ infection (by site)Cost-effectiveness at six months

### Statistical analyses

Descriptive and summary statistics will be calculated by treatment group and stratum (pre-hospital and emergency department region) for baseline characteristics. Continuous data will be summarised as means (standard deviations) or medians (interquartile ranges) for non-normal data and categorical data by counts and proportions. The number of screened patients who fulfilled study inclusion criteria and the number included in the primary and secondary analyses as well as all reasons for exclusions in primary and secondary analyses will be reported.

The main primary and secondary analyses will follow an ITT approach to define the full analysis patient set, based on all randomly assigned patients after the eight-patient run-in period, except those withdrawing consent for use of all trial data and those not fulfilling inclusion criteria and never receiving the intervention [20, 29].

The early intervention design of the POLAR study specifically anticipates incomplete adherence to assigned cooling treatment in the complex clinical context of the study cohort. It is expected that the main reason for incomplete compliance with cooling will be due to the effects of alcohol or other drugs confounding assessment of TBI severity at the time of randomisation, leading to inclusion of patients with impaired consciousness not due to severe TBI for whom ongoing cooling may be clinically unwarranted. Other anticipated reasons include extracranial trauma and coincident haemorrhage for which cooling may be at least temporarily undesirable in the context of a patient’s overall clinical condition.

#### Primary outcome

The primary outcome, the midpoint dichotomised GOSE, will be modelled as a binomial random variable, with a null hypothesis of equality between hypothermic and standard therapy groups in the proportion of subjects with an unfavourable outcome. This will be assessed with an uncorrected Chi-square test applied to the 2 × 2 contingency table comprising the full analysis set of patients according to randomised treatment group. This primary trial outcome will be reported as an unadjusted risk ratio with associated 95% confidence interval (CI) and also as the risk difference with 95% CI and odds ratio with 95% CI. The number needed to treat for benefit or harm will also be reported if a statistically significant difference between treatment groups is demonstrated.

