#### Sensitivity analyses of the primary and secondary outcomes

Sensitivity analyses of the primary and secondary outcomes will be performed using regression models adjusting for pre-specified baseline covariates as well as any covariate exhibiting substantial imbalance between randomisation arms, as recommended [37]. Linear and generalised linear model diagnostics, outlier assessment and remedial measures will follow standard approaches [30, 38].

Proportionality in ordinal logistic regression models will be assessed [39]. Also, the proportional hazards assumption across treatment arms in time-to-event analyses will be evaluated using scaled Schoenfeld residuals [40] and visual assessment of log-log plots.

Baseline variables to be included as fixed effects when developing adjusted outcomes models comprise the following:Geographic region (Australia and New Zealand, Middle East, Europe – three level nominal categorical)Age (integer values centred on overall median age of trial patients)GCS (integer values with a possible range of 3–15)Pupil reactivity (ordinal, three levels)Hypoxia (binary)Hypotension (binary)Marshall CT brain scan classification (nominal categorical, six levels) [39]Core temperature closest to time of randomisation (continuous)

Generalised linear mixed regression models will be applied with the same fixed effects covariate set while also incorporating as a random effect the multiple randomisation strata comprising hospital and pre-hospital research groups. In the event the above regression models do not accommodate the number of pre-specified covariates, sensitivity analyses will be simplified to adjust at least for POLAR treatment and the baseline extended IMPACT TBI probability of 6 month unfavourable outcome.

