### Sample size, power and interim analysis schedule

The overall recruitment target was set at 500 participants from commencement in December 2010 and was slightly increased to 510 participants in September 2017 after blinded review of the combined proportion of patients with ‘consent withdrawn’ or ‘loss to follow-up’. A total of 511 patients were randomised before the conclusion of trial recruitment on 10 November 2017.

A study of fixed size with full compliance and follow-up would require 364 patients (182 in each of two treatment arms) to detect a 15% absolute increase from 50% to 65% in favourable neurological outcome at six months following injury (equivalent to a 30% relative improvement in risk) with slightly > 80% (82.8%) power, assuming a two-sided alpha of 0.05 and an uncorrected Chi square test. This postulated POLAR risk improvement from a baseline of 50% to 65% in treated patients is equivalent to an odds ratio of approximately 1.86.

The original POLAR trial sample size of 364 fully evaluable patients was appropriately inflated to a practically required target of 500 patients to maintain 80% power to find the anticipated beneficial effect of prophylactic hypothermia while accommodating anticipated losses to follow-up (5%) and non-compliance (cross-over from cooling to control and related losses, maximum 12%). Also incorporated was a much smaller (0.7%) inflation necessary to accommodate the originally anticipated interim analyses of both mortality and the proportion of unfavourable neurological outcomes using Haybittle-Peto 3SD group sequential boundaries at two recruitment points (one-quarter [*n* = 125] and one-half [*n* = 250]) [7].

Following the October 2015 publication of the EUROTHERM3235 study [6], the POLAR DSMC required a further substantial increase in interim monitoring, namely at increments of 50 patients from *n* = 300 to *n* = 450 inclusive. Ten of 11 planned interim analyses will be of both mortality and the proportion of unfavourable neurological outcomes, while at the penultimate (*n* = 450) assessment, short-term 28-day mortality alone will be assessed due to time constraints. These extra analyses implied a sample size inflationary requirement (4% - 0.7% = 3.3% extra) [44] which may be accommodated within the originally planned sample size, provided losses to follow-up and non-compliance remained below anticipated limits.

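### The primary chi-square test is valid and matches the sizing, but it is unadjusted: precision from baseline covariates and strata is left to sensitivity analyses that cannot drive the conclusion

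*SAP article*

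**What the plan says.** - **Primary test and estimate** (SAP article, Statistical analyses, Primary outcome): "This will be assessed with an uncorrected Chi-square test applied to the" 2 × 2 table of the full analysis set, by randomised arm. "This primary trial outcome will be reported as an unadjusted risk ratio", with a risk difference and an odds ratio alongside. No stratum or covariate enters.
- **Randomisation** (Randomisation, Table 2): the schedule was "stratified by hospital group or pre-hospital paramedic ambulance service with a permuted block scheme". Table 2 numbers 13 strata, four pre-hospital and nine hospital.
- **Adjustment** (Sensitivity analyses of the primary and secondary outcomes): eight baseline variables are named: region, age, GCS, pupil reactivity, hypoxia, hypotension, Marshall class and core temperature. To these the plan adds "as well as any covariate exhibiting substantial imbalance between randomisation arms, as recommended". A mixed model with the randomisation strata as a random effect is also planned. If the models cannot carry the covariates, the fallback adjusts at least for treatment and the extended IMPACT probability of unfavourable outcome.
- **Sizing** (Sample size, power and interim analysis schedule): 182 per arm "to detect a 15% absolute increase from 50% to 65% in favourable neurological outcome at six months", with "slightly > 80% (82.8%) power", "assuming a two-sided alpha of 0.05 and an uncorrected Chi square test".
- **What decides the trial** (same section): the conclusions are tied to the primary analysis in the ITT set, and the final critical value is 1.996 (P = 0.0459).

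**The concern.** The plan treats age, GCS, pupils and an IMPACT probability as predictors of outcome, since it builds its adjusted models from them. They are already being collected. An analysis of a binary outcome that conditions on strong predictors estimates the treatment effect more precisely, yet here that analysis can only accompany the headline result.

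Recruitment closed at 511, so efficiency in the analysis is the main remaining way to protect power. The plan says the extra interim looks fit within the sample size only if losses and non-compliance stay below the anticipated limits.

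A second, smaller issue concerns the adjusted model itself. The imbalance clause has no threshold and no candidate list, so the final covariate set is not known until the arms have been compared.

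**Working it through.** **1. Reproduce the stated power.** Inputs from the sample-size section: n = 182 per arm, 0.50 v 0.65, two-sided 0.05. Power = Φ{[δ√n − z√(2p̄q̄)] / √(p₁q₁ + p₂q₂)}.
- p̄ = 0.575, so √(2 × 0.575 × 0.425) = 0.6991
- √(0.25 + 0.2275) = 0.6910
- (0.15 × √182 − 1.96 × 0.6991) / 0.6910 = (2.0236 − 1.3702) / 0.6910 = 0.946, and Φ = 82.8%. This matches.

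With 183 per arm and z = 1.996 the formula gives 82.0%, against 82.3% stated from design software, which is close enough. 364 / 0.95 / 0.88² × 1.007 = 498, consistent with the target of 500.

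**2. Unadjusted power at the achieved size, under the plan's own allowances.** 511 × 0.95 ≈ 485 evaluable. A 15-point effect diluted by 12% is 15 × 0.88 = 13.2 points, so 50% v 63.2%. With 242.5 per arm and z = 1.996:
- (0.132 × √242.5 − 1.996 × 0.7009) / 0.6947 = (2.0556 − 1.3990) / 0.6947 = 0.945, and Φ = 82.8%.

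The chi-square therefore still delivers about its planned power.

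**3. What adjustment and stratification would change, N = 364, z = 1.96.** The documents give neither the covariates' prognostic strength nor the size of stratum effects, so both are assumed over a range. Simulation: 13 unequal strata, permuted blocks of 4, one prognostic score, and marginal rates centred on 50% v 65%. There were 6,000 runs per cell (Monte Carlo SE about 0.5 points for power, 0.3 for type I error). CMH is the Cochran-Mantel-Haenszel test on the 13 strata. The logistic model adjusts for the score only.

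| Score AUC | Stratum SD (log-odds) | Chi-square power | CMH power | Logistic power | Chi-square type I error |
|---|---|---|---|---|---|
| none | 0 | 82.5% | 82.3% | 82.5% | 5.1% |
| 0.63 | 0.3 | 83.3% | 83.5% | 84.9% | 5.2% |
| 0.72 | 0.3 | 83.3% | 83.5% | 88.0% | 5.4% |
| 0.78 | 0.3 | 83.2% | 83.1% | 92.0% | 5.0% |
| 0.84 | 0.5 | 83.5% | 83.8% | 95.1% | 4.8% |
| none | 0.5 | 84.5% | 85.5% | 84.0% | 4.8% |
| none | 1.0 | 85.0% | 88.6% | 84.6% | 3.4% |

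- Covariate gain: 84.9 − 83.3 = 1.6 points at the low end, and 95.1 − 83.5 = 11.6 at the high end.
- Stratum-only gain: −0.1 to +0.3 points in the four rows with a score, 1.0 at SD 0.5 and 3.6 at SD 1.0.
- Chi-square type I error is not materially inflated in any row. At SD 1.0 it falls to 3.4%, which is conservative.

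**4. The same question on the risk-difference scale, N = 485, 50% v 63.2%, z = 1.996.** Here the logistic model is standardised to a marginal risk difference with robust standard errors (4,000 runs per setting).

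| AUC | Chi-square power | Standardised power | Variance ratio |
|---|---|---|---|
| 0.63 | 82.9% | 85.6% | 1.07 |
| 0.70 | 82.3% | 87.5% | 1.13 |
| 0.74 | 82.4% | 89.1% | 1.21 |
| 0.79 | 81.9% | 91.9% | 1.31 |
| 0.82 | 82.8% | 94.5% | 1.47 |

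Both estimators average about 0.13, so the estimand is unchanged. Type I error of the adjusted test is 4.5% to 5.3% against a nominal 4.6% (Monte Carlo SE about 0.3 points).

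**5. Can the data carry the model?** Treatment (1), strata (12), age (1), GCS (1) and pupils (2) make 17 terms. Expected unfavourable outcomes are 485 × (1 − 0.566) ≈ 210, or about 12 per term. This is workable, but individual strata may be sparse.

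**The case against.** The strongest reply is that nothing here is wrong. The chi-square is pre-specified, fully defined and the test used for sizing, and it keeps about 82% to 83% power after the planned allowances. Adjusted estimates will be reported beside it. Changing the primary analysis after recruitment has closed is more than an edit, and the gain rests on assumed AUCs with a correctly specified predictor and no missing data. All of this stands, and it limits the point to efficiency. It does not remove the point: the change needs no new patients or data, and six-month outcomes were still being collected when the plan was written.

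Several stronger readings are tempting, but the document does not support them:
- **That ignoring the strata invalidates the test.** It makes the test conservative at worst, and the strata do enter a planned mixed model.
- **That the adjusted covariates are chosen from the data.** Eight are named in advance. Only the imbalance add-on and the undefined trigger for the fallback depend on the data.
- **That the fallback abandons adjustment.** It keeps prognostic adjustment through the IMPACT probability.
- **That the adjusted primary model will fail to converge under a log or identity link.** Those links are named for the secondary binary outcomes. The sensitivity section fixes no link for the adjusted primary model.
- **That chance imbalance biases the headline estimate.** The test's error rate and confidence interval already allow for it. What is lost is precision.

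**Conclusion.** The point holds as an efficiency weakness that should be corrected, and not as an error or contradiction. The analysis that decides the trial uses none of the baseline information that the plan itself regards as prognostic.

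Under assumed AUCs of 0.63 to 0.84, adjustment is worth roughly 2 to 12 points of power. For AUCs of 0.63 to 0.82, the reduction in variance on the risk-difference scale is equivalent to about 7% to 47% more patients. Nearly all of this comes from the covariates, with the strata alone worth about 0 to 4 points.

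The direction is secure: every assumed AUC showed a gain. The size is not, because it depends on prognostic strength that the documents do not give and on a single well-specified score. A model with strata and several covariates together was not simulated. The imbalance clause is a separate, lesser defect confined to sensitivity analyses.

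**What to change.** Before unblinding:
- Make the primary analysis a logistic model with treatment, randomisation stratum (collapsed by a stated rule if sparse) and a fixed covariate set from the existing list: at least age, GCS and pupil reactivity, or the IMPACT probability in their place.
- Standardise over the trial population to report a marginal risk ratio and risk difference with robust standard errors, and test at 1.996. Standardisation matters because the model's conditional odds ratio is a different estimand.
- Keep the chi-square and unadjusted estimates as supportive.
- Delete "as well as any covariate exhibiting substantial imbalance between randomisation arms, as recommended" from the sensitivity section, and state what triggers the IMPACT fallback.
- State a simple rule for missing baseline values.

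The cost is a dated amendment and modest programming, with no new data. The downsides are slight model dependence, handling of a few missing baseline values, and a boundary that was derived for the chi-square comparison, so that its use with the adjusted statistic should be stated explicitly.
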